## Methods

### Research Design

This study is developmental research involving the systematic and conceptual design of a psychological treatment approach. The development model that will be used as the basis for this research activity is one adapted from the ADDIE (Analysis, Design, Development, Implementation, and Evaluation) model [42,43]. A prospective, parallel randomized controlled trial design involving pre- and posttesting of a treatment group and a control group will be used by the researchers [44]. At the end of a diagnostic interview conducted by the researchers, participants who are considered eligible for the study will be randomly assigned to 1 of 2 groups: the web-based CBT group or the usual care control group.

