### Research Subjects

The research subjects will consist of female adolescent students in Indonesia and South Africa (aged 15-17 years); 118 people from each country will be recruited from general practice or family medicine clinics as well as high schools within each study area to arrive at an overall sample of 236 participants for this study. An initial assessment will be conducted on 1000 potential participants (500 adolescent girls per country), who will be screened according to the research criteria so that a representative sample for the intervention may be obtained. The results of a recent study [45] found that 44.1% of participants were able to complete a CBT program using a web-based approach and that the average completion rate for the 12 sessions was 7.8 (65%). Therefore, we will take into account the attrition rate of 55.9% by including 55.9% extra participants in our initial sample for each group produced by the G*power (Heinrich-Heine-Universität Düsseldorf) sampling program [46]. To account for the potential effects of missed sessions in a standard web-based CBT program, as shown by recent research [45], 4.2 sessions (35%) will be added to the 12-session program, which will result in approximately 16 sessions (to be delivered over 4 months). Based on the G*power calculation, the required sample size is 38 participants per group (85% statistical power; medium effect size Cohen *d*=0.5; a priori probability level of 0.5) for a linear mixed model (LMM) analysis. Given the presumed attrition rate, we will recruit 59 participants per group in each country.

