### Data Analyses

The analyses of the data in this study will include descriptive analysis, analysis of the coefficient of agreement between program raters (interrater reliability), and internal consistency analysis using Cronbach α and partial η^2^ (effect size statistics). A sensitivity analysis will also be carried out to avert potential data dredging. The Mauchly sphericity test and Levene equality of variance test will be carried out to ensure that the assumptions of the chosen statistical test are met. LMM will be used to analyze the primary outcome measures statistically based on the principle of intention-to-treat to determine whether considerable changes have occurred over time [51]. By using LMM, participants with incomplete data will be included in the analyses so that treatment effects can be assessed over time (group time interaction) [51]. Using LMM, the treatment group, time, and interactions between the treatment group and time will be considered fixed factors; the covariance structure will be constructed in an unstructured manner. We will ascertain posttest outcomes in terms of mean changes in GAD-7 and FGI-Checklist scores from baseline to 4 months following the pretest. Complier-adjusted causal effect (CACE) analysis will be conducted based on the causal framework and estimation methods to account for variations in treatment effect due to variations in treatment adherence between the groups [51,52]. We will calculate CACE as the difference between the mean GAD-7 and FGI-Checklist scores of compliers in the treatment group as well as the control group. To be considered a complier, a participant must have attended 80% or more of the program sessions, which is a frequently used threshold [51,53]. A bootstrapping technique will be used to determine standard errors. Statistical analyses will be completed using R (R Core Team) to analyze the CACE data and SPSS (version 29; IBM Corp) for the rest of the analyses. *P* values of .05 or less will be considered statistically significant.

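### The primary mixed model gives each randomised arm its own baseline mean; constraining the arms to a common baseline would estimate the same effect at least as precisely, at no cost in data

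*Protocol article*

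**What the plan says.** The Research Design section describes a parallel randomised trial "involving pre- and posttesting of a treatment group and a control group", so each outcome has two assessment times. The Data Analyses section names the mean structure of the primary model: "the treatment group, time, and interactions between the treatment group and time will be considered fixed factors". It adds that "the covariance structure will be constructed in an unstructured manner". The treatment effect is taken from the group-by-time interaction, and the outcome is expressed as a change score: "We will ascertain posttest outcomes in terms of mean changes in GAD-7 and FGI-Checklist scores from baseline to 4 months following the pretest".

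The article nowhere enters the baseline score as a covariate or holds the two arms to one baseline mean. The reporting of medication changes described in the Discussion concerns confounding and is not baseline adjustment. The fixed-effects list is stated, so this point is about a choice the article makes, not about a detail left to an unseen analysis plan.

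**The concern.** With two times, two arms and free effects for group, time and their interaction, the model fits four separate means. On complete data, whatever the covariance structure, the interaction is then exactly the treatment arm's mean change minus the control arm's mean change. The group main effect allows the arms to differ at baseline, although randomisation guarantees that they do not differ in expectation. Any baseline difference in the sample is chance, and the change score carries that chance difference into the estimate.

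A model that knows the baseline means are equal uses the pretest only to explain variation in the posttest. It targets the same quantity. At stake are the width of the confidence interval and the power of the trial. The validity of the estimate is not in question, since both estimators are unbiased under randomisation.

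**Working it through.** **The plan's own figure.** The article gives no variance or correlation for the primary comparison. Its only related figure is the sample size in Research Subjects: 38 per group for "medium effect size Cohen *d*=0.5" and "85% statistical power". A two-sample comparison at two-sided 0.05 needs 72 per group (normal approximation) or 73 (t-test), so 38 does not reproduce. It does arise as the n of a paired t-test. It also arises as the total N of a within-between interaction test with f = 0.25 and correlation 0.5, but the article does not say that either was used. The value of r on which the design rests therefore cannot be recovered, and r is treated as an assumption below. The sample size itself is a separate matter.

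**Inputs.**
- From the article: two assessments; 59 per group per country; 55.9% attrition; moderate to severe symptoms required at baseline.
- Assumed: r = 0.3, 0.5 or 0.7 in unselected girls; unselected SD = 1 at both times; a linear relation between pretest and posttest.

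**General formula.** Let b be the slope of posttest on pretest, s² the residual variance and v the baseline variance in the enrolled sample. Per participant:
- difference in change (stated model): s² + (1 − b)²v
- common baseline mean: s² (large-sample)
- variance ratio: s² / [s² + (1 − b)²v]

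The term (1 − b)²v cannot be negative, so the ratio never exceeds 1.

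**Case 1: equal SDs, complete data.** Here b = r, s² = 1 − r² and v = 1. The stated model's variance is 2(1 − r), and the ratio reduces to (1 − r²)/[2(1 − r)] = (1 + r)/2.

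| r | stated model | common baseline | ratio |
|---|---|---|---|
| 0.3 | 1.40 | 0.91 | 0.65 |
| 0.5 | 1.00 | 0.75 | 0.75 |
| 0.7 | 0.60 | 0.51 | 0.85 |

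For d = 0.5 at two-sided 0.05 with 59 per group (normal approximation), power moves from 63% to 81%, from 77.5% to 88% and from 94% to 97%.

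Two numerical checks used 38 per group. In one simulated data set at r = 0.5, generalised least squares gave an interaction of −0.5646, identical to the raw difference in mean change. Its standard error was 0.229, against 0.199 with a common baseline. Over 20,000 simulated trials at each r, comparing the change score with baseline adjustment by ANCOVA, the variance ratios were 0.655, 0.755 and 0.864. Both estimators averaged −0.50. The slight excess over the formula is in line with the small cost of estimating the slope.

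**Case 2: eligibility truncates the same baseline score, complete data.** Selection on the pretest leaves b and s² unchanged and shrinks v. For a normal score with the top fraction p entering, v = 1 + zλ − λ², where z is the cut-off and λ = φ(z)/p. This gives v = 0.363 for p = 50% and v = 0.264 for p = 30%.

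| r (unselected) | p = 50% | p = 30% |
|---|---|---|
| 0.3 | 0.91/(0.91 + 0.178) = 0.84 | 0.91/(0.91 + 0.130) = 0.88 |
| 0.5 | 0.75/(0.75 + 0.091) = 0.89 | 0.75/(0.75 + 0.066) = 0.92 |
| 0.7 | 0.51/(0.51 + 0.033) = 0.94 | 0.51/(0.51 + 0.024) = 0.96 |

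**Case 3: 55.9% of posttests also missing.** Of 59 participants, 59 × 0.441 = 26 have a posttest. The residual part is then averaged over 26 and the baseline part over 59, so the ratio becomes s² / [s² + (26/59)(1 − b)²v].

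| r (unselected) | no truncation | p = 50% | p = 30% |
|---|---|---|---|
| 0.3 | 0.81 | 0.92 | 0.94 |
| 0.5 | 0.87 | 0.95 | 0.96 |
| 0.7 | 0.93 | 0.97 | 0.98 |

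**The case against.** The strongest reply is that the stated model is a standard, unbiased analysis that contradicts nothing, and that the benefit rests on a correlation the article does not give. This stands as a limit on how hard the point can be pressed: it is an improvement in precision, not the repair of an error. It does not remove the point, because the fixed effects are fixed in the text and the direction of the gain does not depend on r.

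The reply also stands on size. A reader might take (1 + r)/2 as the expected gain, equivalent to 18% to 54% more participants (1/0.85 to 1/0.65). That is the equal-SD, complete-data case and marks the upper end.

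A reader might also infer that enrolling only girls with moderate to severe symptoms makes the change score worse, because it lowers r. That does not follow. Selection on the pretest lowers r by shrinking the baseline variance, and that variance is what multiplies the change score's excess. The loss therefore becomes smaller, as Case 2 shows. Putting the lowered r into (1 + r)/2 would misuse a formula that needs equal SDs.

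Nor does the article show that the primary analysis is underpowered because of this choice. Power depends on the unstated r, and the model is not said to be fitted separately by country. With 118 per group pooled and complete data, the stated model has 90% power at r = 0.3 and 97% at r = 0.5. The 55.9% is a programme non-completion figure, so Case 3 is a pessimistic scenario, not a forecast of missing posttests.

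Finally, keeping participants with incomplete data is not an advantage of the change, since the stated mixed model already keeps them.

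**Conclusion.** The point holds as a free improvement in precision. For the same data and the same effect, a common-baseline model has a large-sample variance no larger than that of the stated model. The variance ratio is 0.65 to 0.85 with equal SDs and complete data. It is about 0.84 to 0.96 if eligibility truncates the same baseline score with the top 30% to 50% entering, and about 0.92 to 0.98 if 55.9% of posttests are also missing.

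These ranges assume r between 0.3 and 0.7, normal scores and a linear relation. The article does not say whether the eligibility assessment and the pretest are the same score, so it cannot settle which case applies. At the 0.98 end, the small cost of estimating the slope could absorb most of the gain. Bias, invalidity or a demonstrated power failure should not be read into it.

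**What to change.** In Data Analyses, replace the fixed-effects sentence with a mixed model that has a common baseline mean: terms for time, treatment group at posttest only, and country, with the unstructured covariance retained and no group main effect. State that the treatment effect is the between-group difference at 4 months, reported with its 95% CI, for the GAD-7 and the FGI-Checklist alike. Mean changes by arm can still be shown descriptively.

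ANCOVA on the 4-month score with the baseline score as covariate is the second choice. It gives a similar estimate, but only among participants with a posttest, so it drops participants whom the stated mixed model keeps.

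The cost is one or two sentences in the analysis section. No extra participants, assessments or software are needed, and the change should be made before outcome data are examined by arm.

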### Treatment Activities and Procedures

This research will be reported in line with the guidelines for the Consolidated Standards of Reporting Trials (CONSORT) [48]. The study was registered in a clinical trials registry before the recruitment of the first participant. A 16-session CBT manual incorporating web-based counseling techniques and principles and local wisdom approaches to the treatment of GAD among adolescent college girls with FGID symptoms will be developed by the research team for this study. The research team will adapt evidence-based techniques and procedures from existing CBT intervention manuals for GAD and FGID treatments with a focus on cultural components, traditions and values, and local wisdom, as well as web-based counseling techniques and processes, to address GAD and FGID symptoms among adolescent college girls. Each web-based session for the treatment group as well as the usual care session for the control group in each country (study site) is expected to last for 90 minutes each, once a week for 4 months. To assess the efficacy of CBT combined with local wisdom and web-based counseling approaches, we used the usual care as a comparison group. This study defines usual care as whichever treatment for GAD and FGIDs adolescents receive from their regular health care providers or therapists. This form of comparison group was selected to appraise the effects of CBT combined with local wisdom and web-based counseling approaches against the treatments that would normally be available without this intervention. The use of usual care as a comparison group also contributes to the viability of the trial since other clinicians are not required to be trained in a particular approach to comparator therapy. Due to this study’s design, it is possible to compare the effects of CBT combined with local wisdom and web-based counseling methods with the usual practice in GAD treatment for adolescent girls with FGIDs. Three specialist raters in each country will evaluate the treatment’s integrity. During the project, 2 postgraduate-level psychologists with a master’s degree will serve as research assistants in each country. Two cognitive behavioral therapists with a doctorate in counseling psychology will provide the web-based CBT intervention for the treatment group, while the usual care intervention for the control group in each country will be provided by 2 CBT practitioners with doctorate degrees in psychology. The recruitment process will begin in July 2023, and the trial will begin in August 2023. The posttest assessment data gathering will be undertaken by November 2023. A summary of the treatment intervention is shown in Table 1.

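### The CACE is defined on mean scores with no time point or pretest, while the main outcome is change from baseline: a minor loss of precision and comparability

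*Protocol article*

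**What the plan says.** All the relevant text is in the Data Analyses section of the protocol article.

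- **Main outcome:** "We will ascertain posttest outcomes in terms of mean changes in GAD-7 and FGI-Checklist scores from baseline to 4 months following the pretest".
- **Main model:** a linear mixed model (LMM) under intention to treat, in which "the treatment group, time, and interactions between the treatment group and time will be considered fixed factors". The Research Design section describes pre- and posttesting, so with two occasions the interaction is the between-arm difference in mean change.
- **CACE:** "We will calculate CACE as the difference between the mean GAD-7 and FGI-Checklist scores of compliers", compared between the two arms. The sentence names no change, occasion or covariate.
- **Method behind the CACE:** the "analysis will be conducted based on the causal framework and estimation methods to account for variations in treatment effect" arising from differing adherence, with citations. The estimator is not described further, except that standard errors will be bootstrapped.
- **Complier:** "a participant must have attended 80% or more of the program sessions".

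The control arm also has sessions. The Treatment Activities and Procedures section says "the usual care session for the control group in each country (study site) is expected to last for 90 minutes each", weekly for 4 months, so attendance can be observed in both arms.

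**The concern.** The same two scales are given two outcome definitions a few lines apart. The main definition subtracts the pretest. The CACE definition, taken as written, does not use it.

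The CACE is there to show how the treatment effect varies with adherence, so readers will set it beside the ITT estimate. If the two rest on different outcomes, part of any gap between them reflects how baseline was handled rather than adherence. Leaving out a prognostic pretest also widens the interval of an analysis that is already imprecise, because only a fraction of participants are likely to be compliers. And an outcome that is not fixed in advance leaves a choice of scale open until after the data are seen.

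**Working it through.** The plan gives no figure for the CACE, so there is none to reproduce. The check takes the literal wording and asks what it costs.

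**Inputs from the protocol article:** 118 per arm (59 per arm in each of two countries, Randomization and Masking); planned effect d = 0.5 and a cited 44.1% completion rate for web-based CBT (Research Subjects).

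**Assumptions:** 44.1% stands in for the share meeting the 80% attendance rule; all 118 per arm are observed; SD is 1 at both occasions; the pre-post correlation r is 0.3, 0.5 or 0.7; the effect is -0.5 SD in compliers and zero in others.

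**Step 1. The two definitions side by side.**
- Main: (post - pre) in the treatment arm minus (post - pre) in the control arm.
- CACE as written: mean score of treatment compliers minus mean score of control compliers.

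**Step 2. Randomisation-based CACE: expectation.** Take CACE = ITT difference / complier share. Randomisation makes the expected baseline difference zero, so the score and change versions target the same quantity. In simulation (true value -0.50 SD) the score version averages -0.50 to -0.52 and the change version -0.49 to -0.52. There is no systematic bias.

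**Step 3. Randomisation-based CACE: a single trial.** The two versions differ by (chance baseline difference) / (complier share).
- SE of the baseline difference = sqrt(2/118) = 0.130 SD.
- Its mean absolute value = 0.130 x sqrt(2/pi) = 0.130 x 0.798 = 0.104 SD.
- Divided by 0.441, this gives 0.236, or about 0.24 SD, whatever r is. Simulation gives the same.
- Against the planned effect: 0.24 / 0.5 = 48%.

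**Step 4. Precision.** To a first approximation, SE = k x sqrt(2/118) / 0.441 = k x 0.295, where k = 1 for the score, sqrt(2(1 - r)) for change and sqrt(1 - r^2) for the baseline-adjusted score.

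| r | score | change | adjusted (formula) | adjusted (simulated) |
|---|---|---|---|---|
| 0.3 | 0.30 | 0.35 | 0.954 x 0.295 = 0.28 | 0.29 |
| 0.5 | 0.30 | 0.30 | 0.866 x 0.295 = 0.26 | 0.26 |
| 0.7 | 0.30 | 0.23 | 0.714 x 0.295 = 0.21 | 0.22 |

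The adjusted version has the smallest SE at each r. Using the simulated values, the gain over the score is 1 - 0.29/0.30 = 3%, 1 - 0.26/0.30 = 13% and 1 - 0.22/0.30 = 27%. Change scores do worse than the plain score at r = 0.3.

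**Step 5. Attenders compared directly.** This is the literal reading of the sentence. With no treatment effect, an unadjusted score contrast is off by r x (baseline gap between the attender groups). Assume that treatment-arm attendance falls with baseline severity (log-odds -0.7 per SD), that control attendance does not depend on it, and that about 44% comply. Simulated contrasts under no effect:

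| r | score | change | baseline-adjusted |
|---|---|---|---|
| 0.5 | -0.17 | +0.18 | 0.00 |
| 0.7 | -0.25 | +0.10 | 0.00 |

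The implied baseline gap is about -0.35 SD (-0.17/0.5 = -0.34; -0.25/0.7 = -0.36). If attendance depends on baseline in the same way in both arms, there is no systematic gap and these biases vanish. The adjusted 0.00 follows from the assumption that selection works only through the measured pretest.

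**The case against.** The strongest reply is that the CACE sentence never says the scores are unadjusted. It closely follows a sentence that defines outcomes as changes, so it may be shorthand for them. It also rests on cited estimation methods that are not shown, and a condensed article may leave covariates to the full analysis plan. This stands in part: the shorthand reading cannot be excluded. But the sentence is an explicit rule of calculation rather than a silence, and shortly before it the authors write "mean changes in GAD-7 and FGI-Checklist scores from baseline to 4 months following the pretest" when they mean changes. Even on the shorthand reading, baseline-adjusted scores would be more precise than changes.

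A reader might infer two stronger points, which the documents do not support.

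- *The CACE cannot be set beside the ITT effect.* Under randomisation the score and change versions have the same expectation. The CACE differs from the ITT effect by design, because it concerns compliers. What suffers is the cleanness of the comparison within one trial.
- *The CACE carries systematic baseline differences because of its outcome.* The -0.17 and -0.25 SD come from comparing groups selected on attendance after randomisation, under an assumed attendance model that differs between arms. That is a separate and more serious weakness of the complier contrast. Change scores do not repair it. Baseline adjustment removes only the part due to measured severity, not selection through unmeasured causes such as motivation.

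**Conclusion.** The point holds as a minor one. The plan does not fix the CACE outcome consistently with the main outcome and, read literally, leaves the pretest unused. With a randomisation-based CACE the cost is chance imbalance (about 0.24 SD on average between the score and change versions in one trial) and an SE of about 0.30 where 0.29, 0.26 or 0.22 is attainable. With a direct comparison of attenders there can also be bias, about -0.17 to -0.25 SD under the model assumed here and none if attendance depends on baseline alike in both arms.

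These sizes rest on 118 observed per arm, 44.1% compliers and the assumed correlations. With the attrition the plan expects, the chance imbalance and the SEs would both be larger. The intention-to-treat LMM is unaffected.

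**What to change.** In the Data Analyses section, define the CACE outcome as the 4-month GAD-7 score and the 4-month FGI-Checklist score, each with its own pretest value as a covariate, and refit that model within every bootstrap sample. Beside it, report a supplementary ITT estimate on the same baseline-adjusted 4-month scale, so that the two can be compared like with like. The group-by-time LMM can stay as the main analysis.

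The cost is one sentence in the plan, one covariate in the R code and one supplementary ITT estimate. No new data are needed. This change does not settle which participants the CACE should compare, and that has to be dealt with separately.

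### The CACE formula compares attenders with attenders across arms, which is a per-protocol contrast and not a complier effect

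*Protocol article*

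**What the plan says.** All of the relevant rules are in the protocol article. Under Data Analyses, the primary outcomes are analysed by a linear mixed model on the intention-to-treat principle. A second analysis is then added: "Complier-adjusted causal effect (CACE) analysis will be conducted based on the causal framework and estimation methods". Its purpose is "to account for variations in treatment effect due to variations in treatment adherence between the groups". The calculation is fixed in one sentence: the team will "calculate CACE as the difference between the mean GAD-7 and FGI-Checklist scores of compliers in the treatment group as well as the control group". The next sentence defines the subgroup: "To be considered a complier, a participant must have attended 80% or more of the program sessions". Standard errors come from a bootstrap, and R is reserved for this analysis.

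Under Treatment Activities and Procedures, both arms have a weekly timetable; the duration is set for "Each web-based session for the treatment group as well as the usual care session for the control group". The content of the control arm is different: "This study defines usual care as whichever treatment for GAD and FGIDs adolescents receive from their regular health care providers or therapists". The eligibility criteria also call the control condition a usual care program, so the word program is not reserved for CBT.

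Under Research Subjects, the article reports from an earlier study that "44.1% of participants were able to complete a CBT program using a web-based approach". It gives no expected attendance for usual care.

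**The concern.** A complier average causal effect compares treated participants who comply with control participants who would have complied had they been assigned to the programme. The second group cannot be seen in the data. It has to be recovered indirectly, usually by using randomisation as an instrument.

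The article does something else. It applies an observed attendance rule to any participant and subtracts the two subgroup means. Attending usual care does not show that a control participant would have attended web-based CBT. The two subgroups are therefore selected on different behaviours, both of which occur after randomisation. A bootstrap measures the sampling error of that difference but does not remove the selection.

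At stake is the interpretation of the only adherence analysis that the article names. It would be reported as causal although randomisation does not protect it, and it could show an effect where none exists, or hide or exaggerate a real one.

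**Working it through.** **Step 1: the two readings of the complier rule.** The article states no CACE figure, so there is none to reproduce.

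- *Program sessions means the sessions of one's own arm.* Attendance is then observable in both arms, and the formula is CBT attenders minus usual-care attenders.
- *Program sessions means CBT sessions only.* Control participants attend none, so no control complier is observed and the stated mean does not exist.

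Neither reading gives a CACE.

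**Step 2: size of the bias under the first reading.** Inputs:

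- CBT attendance p_T = 0.441. This is an assumption: it is the earlier study's completion rate for a 12-session programme, used as a proxy.
- Usual-care attendance p_C = 0.80, varied below. This is an assumption and is not in the article.
- Correlation of adherence with improvement, rho = 0.3. This is an assumption and is not in the article.
- True treatment effect = 0.

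If adherence is a normal latent variable cut at the threshold c that leaves a proportion p above it, the mean among attenders is shifted by rho × phi(c)/p. The spurious advantage of CBT is

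bias = rho × [phi(c_T)/p_T − phi(c_C)/p_C].

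- p_T = 0.441: c = 0.148, phi = 0.3946, ratio = 0.895.
- p_C = 0.80: c = −0.842, phi = 0.2800, ratio = 0.350.
- Difference = 0.545, and 0.3 × 0.545 = 0.163 SD.

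A second selection model lets the prognostic trait correlate 0.3 with outcome but load only 0.7 on attendance (also assumed). The effective correlation is 0.3 × 0.7 = 0.21, and 0.21 × 0.545 = 0.114 SD. A simulation of 2,000,000 participants per scenario under this model also gave 0.114 SD.

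Varying control attendance, with CBT attendance held at 44.1% (positive = spurious benefit of CBT):

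| Usual-care attendance (assumed) | Correlation 0.3 acting directly | Effective correlation 0.21 |
|---|---|---|
| 25% | −0.11 SD | −0.08 SD |
| 44.1% | 0 | 0 |
| 60% | 0.08 SD | 0.05 SD |
| 80% | 0.16 SD | 0.11 SD |
| 95% | 0.24 SD | 0.17 SD |

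The bias is zero when attendance is unrelated to prognosis, or when both arms have the same attendance rate and the same selection mechanism.

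**Step 3: the randomisation-based alternative.** In the same simulation, the intention-to-treat difference divided by the CBT-arm compliance proportion gave values within 0.01 SD of zero when the true effect was zero. It gave 0.49 to 0.51 SD when the true complier effect was 0.50 SD. The simulation assumed that CBT non-compliers gain nothing from assignment and that controls have no access to the programme.

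**Step 4: what happens if the first of those assumptions fails.** Suppose compliers gain 0.50 SD, participants below the cut-off gain 0.25 SD (both assumed), and compliance is 44.1%.

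- Intention-to-treat effect = 0.441 × 0.50 + 0.559 × 0.25 = 0.360 SD.
- Divided by compliance: 0.360/0.441 = 0.82 SD, against a true complier effect of 0.50 SD.

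The alternative therefore carries its own risk when partial attendance is effective.

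**Step 5: precision.** Treating the compliance proportion as known, the standard error is about 1/0.441 = 2.27 times that of the intention-to-treat estimate.

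**The case against.** The strongest defence is that a difference in means between compliers in the two arms is also the textbook definition of the CACE estimand, provided that control compliers are understood as latent. The article invokes a causal framework with citations, sets R aside for this analysis and bootstraps the standard errors, all of which fit a model-based estimator. It is also a condensed article, and estimator detail is commonly left to an analysis plan.

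Part of this stands. The authors may intend a proper estimator, and silence on its details would be no fault. But the article is not silent. It states the calculation and a complier rule based on attendance that actually occurred, and it mentions no latent class or instrument. The control arm has sessions to which that rule can be applied. An analyst following the text would compare attenders with attenders.

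A second objection is that the bias figures rest on assumed inputs. That stands in full. They show what can happen and do not forecast this trial's bias.

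A third is that the instrumental estimate is no safe harbour, because participants below the 80% cut-off may still benefit. That also stands, and the remedy must deal with it.

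A reader might also infer that the 80% threshold is itself wrong, since 0.8 × 16 = 12.8 means 13 sessions in a course extended from 12. The documents do not support that. Table 1 of the article describes a single 16-session curriculum with no separate 12-session core, the article nowhere says that 12 sessions are an adequate dose, and the threshold is pre-specified.

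**Conclusion.** The point holds for the formula as written. It is a per-protocol contrast under a causal name or, if only CBT sessions count, it cannot be calculated.

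Under the labelled assumptions (no true effect, correlation 0.3, attendance of 44.1% and 80%), the spurious effect is about 0.11 to 0.16 SD, depending on the selection model. It can take either sign and can be zero. The article gives neither usual-care attendance nor the prognostic strength of attendance, so direction and size in this trial are unknown.

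A reader might infer that the trial's main conclusion is compromised or that its analysis abandons randomisation. The documents do not support that: the primary outcomes are analysed by an intention-to-treat mixed model, which this problem does not touch, and the CACE is supplementary. Nor do they support saying that a false effect will occur. The point should be fixed before analysis but does not invalidate the trial.

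**What to change.** Replace the formula and the complier sentence with one paragraph that does the following:

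- Defines compliance by attendance at the CBT sessions, in the treatment arm only, keeping the pre-specified 80% threshold.
- Estimates the CACE with randomisation as the instrument, by two-stage least squares with baseline score and country as covariates, or by a principal-stratification model.
- Bootstraps the whole estimator, including the compliance proportion.
- States the exclusion restriction (assignment does nothing for non-compliers) and the assumption that controls have no access to the programme. The second deserves explicit wording, because the article has CBT practitioners delivering the usual-care sessions and lists use of other treatments as a limitation.
- Adds a sensitivity analysis for benefit below the cut-off, for example a lower attendance threshold or sessions attended as a continuous exposure.
- Labels any attender-versus-attender contrast as per-protocol and draws no causal conclusion from it.

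The cost is one paragraph of text. The analysis runs in R, which is already planned for the CACE, and needs only the attendance data that the current rule already requires. The downsides are wider intervals, by a factor of roughly one over the compliance proportion, and reliance on the exclusion restriction.
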